#### Secondary outcomes

The secondary outcome indicators include the residual volume of the bladder, the Spinal Cord Injury-Quality of Life, bladder diary, Neurogenic Bladder Symptom Score, and pudendal nerve electromyography. Besides objective indicators, those outcomes can also reflect the effect of rFMS on NDO-associated symptoms and the Spinal Cord Injury-Quality of Life (SCI-QOL).

Participants with partially voluntary voiding function will be taken bladder residual urine measurements immediately after voiding once a week. Each measurement will scan the bladder in the sagittal and transverse planes. The probe is located on the midline above the symphysis pubis to obtain a sagittal view of the lower abdomen. When the largest picture of the bladder appears on the screen, freeze the image and measure the height (h), depth (d), and cross-sectional area (AS) of the bladder. Then place the probe laterally above the symphysis pubis, at right angles to the sagittal plane, and provide another part of the lower abdomen. When the largest picture appears on the screen, freeze the image and measure the width (w), depth (d), and cross-sectional area (AT) of the bladder. According to previous studies [15], the residual volume is approximately equal to the cross-sectional area of the bladder when measured in the sagittal plane multiplied by the width of the bladder.

SCI-QOL measurement system will assess the quality of life. It includes four aspects: physical health, emotional health, social participation, and physical function [16]. Each aspect has 3–6 sub-items, which can comprehensively evaluate patients’ physical and psychological functions with SCI. SCI-QOL will evaluate the patients at the time of evaluation, and the results will be recorded.

The bladder diary will measure the frequency of acute urinary incontinence, which can reflect the frequency of urinary incontinence and quantify bladder symptoms [17]. Patients will record the frequency of acute urinary incontinence weekly for 8 weeks of the entire trial and during follow-up.

The pudendal nerve and subsacral motor neuron involvement are significantly associated with chronic SCI [18]. Electromyogram (EMG) is the muscle bioelectric pattern recorded with an electromyography instrument. It can evaluate the function of nerves. Studies [19] have found that pudendal nerve stimulation can cause reflex bladder contraction in patients with chronic SCI, which indicates that the function of the pudendal nerve is related to bladder function and can be used to evaluate bladder function. In our study, quantitative external anal sphincter (EAS) muscle electromyography (EMG), pudendal nerve terminal motor latency (PNTML) testing, pudendal somatosensory evoked potentials (PSEP), and bulbocavernosus reflex (BCR) will be measured [20]. The resting and light exertion EMG of EAS will be detected by using concentric needle electrodes [21]. The pudendal nerve terminal motor latency will be recorded by finger cuff electrodes [22]. For pudendal nerve PSEP, the P40 latency will be measured by the recording electrode placing in Cz (active electrode), while the stimulation electrode will be placed in the pubic symphysis [23]. For BCR, mean latency values will be recorded by concentric needle electrodes [24]. Specifically, the patient will be first placed in the lithotomy position, and then the BCR will be elicited by rapidly pressing down on the glans with the probe. Electrodes will be placed around the anus and on the inner thighs at the 3 o’clock and 9 o’clock positions to capture the electrical activity generated by this reflex. Pressure from the probe against the glans generates the initial stimulus waveform. This will be followed by a second elevated waveform or contraction in response to the BCR. Latency will be calculated based on the time between these two events.

Neurogenic Bladder Symptom Score (NBSS) evaluates patients’ symptoms with NB from three dimensions urinary incontinence, storage and urination, and outcome. It is an effective and comprehensive tool for assessing NB symptoms in patients with SCI [25]. NBSS includes three dimensions of urinary incontinence, storage, urination, and outcome, with 24 items, of which two are unscored. The first item is classified according to the patient’s bladder management, and the last item is the patient’s bladder management. The overall quality of life assessment assesses the patient’s urination pattern and quality of life. Each item is worth 0 ~ 3 points or 0 ~ 4 points. The scale’s total score is 74 points, with higher scores indicating more obvious NB symptoms.

### Participant timeline {13}

Before starting the intervention, participant baseline data will be collected, as well as bladder capacity and Pdet measured by urodynamic testing, the residual volume of the bladder, quality of life, bladder diary, NBSS, and pudendal nerve electromyography. After that, interventions will be performed five times a week for 8 consecutive weeks. The bladder compliance (bladder capacity/Pdet) and pudendal nerve electromyography will be evaluated at baseline, 8th week of treatment. The residual volume of the bladder and bladder diary will be recorded once a week during 8 weeks of treatments. SCI-QOL and NBSS will be evaluated at baseline, the 4th and 8th week of treatment. In addition, the above assessments will be followed up at 8 weeks after the end of treatment. The participant timeline is presented in Table 1.

**Table 1 Tab1:** Schedules for follow-up assessments and data collection

		**Study period**					
	**Enrolment**	**Allocation**	**Post-allocation**				**Close-out**
**Timepoint**	*** − t***_***1***_	**0**	***t***_***0***_***: five times a week, for 8 weeks***	***t***_***1***_***: Once a week during 8 weeks of treatments***	***t***_***2***_***: 4th week of treatment***	***t***_***3***_***: 8th week of treatment***	***T***_***4***_***: 8 weeks after the end of treatment***
**Enrolment:**							
**Eligibility screen**	X						
**Informed consent**	X						
**Allocation**		X					
**Interventions:**							
**rFMS and sham stimulation**			X				
**Medication**			X				
**Bladder management strategy**		X					
**Acupuncture treatment**			X				
**Assessments:**							
***Bladder capacity***	X					X	X
***Pdet***	X					X	X
***Bladder compliance***	X					X	X
***Residual volume of the bladder***	X			X			X
***Bladder diary***	X			X			X
***SCI-QOL***	X				X	X	X
***NBSS***	X				X	X	X
***Pudendal nerve electromyography***	X					X	X

### Sample size {14}

Sample size was calculated using bladder compliance as the main outcome. According to the analysis of previous research results [12, 26], bladder compliance change after therapy of 8 ml per cm H_2_O with a standard deviation of 9 ml per cm H_2_O was used in the calculation. Assuming that the standardized effect size is 0.25, the probability of type I error is 5%, and the probability of avoiding type II error is 90%, the trial requires at least 26 participants in each group. Considering the allowable 20% dropout rate, approximately 33 patients per group will eventually be needed.

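### The sample-size paragraph gives two incompatible effect sizes: 8 with SD 9 (0.89 if 8 is a between-group difference) and a standardized effect of 0.25; the stated 26 per group fits the first

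*Protocol article*

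**What the plan says.** Under Sample size {14}, the protocol article bases the calculation on bladder compliance, the primary outcome. The first input is a "bladder compliance change after therapy of 8 ml per cm H_2_O with a standard deviation of 9 ml per cm H_2_O", drawn from two cited sources, and the article says that these figures entered the calculation. The next sentence brings in another effect size: "Assuming that the standardized effect size is 0.25, the probability of type I error is 5" per cent. It adds 90% power, and concludes that "the trial requires at least 26 participants in each group". Allowing for 20% dropout, this becomes about 33 per group.

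The paragraph names no test, no sidedness and no effect-size metric. It does not say whether 8 is a difference between the groups or a change within one group, nor how 0.25 relates to 8 and 9. No other section of the article connects these figures.

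**The concern.** A standardized effect for two means is the difference divided by the standard deviation. With 8 and 9 that is 0.89, which is 3.6 times 0.25. Both values cannot describe the same comparison on the same scale, yet both are given as inputs to a single calculation.

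This paragraph is the only justification for enrolling 66 patients. A reader who takes 0.25 at face value would believe that the trial has 90% power for a small effect. On the inputs that do reproduce 26, it is sized for a difference of about 0.9 SD. A null result could then be misread as excluding a small or moderate benefit. Anyone who checks or reuses the calculation from 0.25 as a mean difference would fail to reproduce it.

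**Working it through.** **Inputs.** All come from Sample size {14} unless noted: difference 8 and SD 9 ml/cmH2O; standardized effect 0.25; alpha 0.05; power 0.90; 26 per group; 20% dropout. The 1:1 allocation is from Trial design {8}. Two assumptions are added because the article is silent: a two-sided test, and 8 as a between-group difference.

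**1. Reproduce the stated figure from 8 and 9.**
- d = 8/9 = 0.889.
- Normal approximation: n per group = 2(1.960 + 1.282)²/d² = 26.6, rounded up to 27.
- Noncentral t: 28 per group.
- One-sided 5%: 22 (normal) or 23 (t).
- Dropout: 26/0.8 = 32.5, rounded up to 33, as stated.

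The stated 26 is therefore what 8 and 9 give under a two-sided test, to within one or two patients.

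**2. Try 0.25 as a standardized mean difference.**
- Normal approximation: 2(1.960 + 1.282)²/0.25² = 336.2, rounded up to 337.
- Noncentral t: 338 per group.
- One-sided 5% (normal): 275.

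None of these is near 26.

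**3. Power at the planned size** (two-sided 5%, noncentral t).

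| Effect d | 26 per group | 33 per group |
|---|---|---|
| 0.889 (8/9) | 88.2% | 94.5% |
| 0.5 | 42.4% | 51.6% |
| 0.25 | 14.3% | 17.0% |

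A one-sided test at d = 0.25 with 26 per group would have about 22 to 23% power.

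**4. Smallest difference detectable with 90% power, 26 per group.** Solving the noncentral t power for d gives 0.917, and 0.917 × 9 = 8.25, about 8.3 ml/cmH2O.

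**5. Try 0.25 as Cohen's f.** For two equal groups f = d/2, so f = 0.25 corresponds to d = 0.5.
- Simple two-group comparison: 86 per group by t-test, not 26.
- Group-by-time interaction in a repeated measures ANOVA: noncentrality = f²·N·m/(1 − ρ), with N the total number, m the number of time points and ρ the within-subject correlation. At N = 52:

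| m | ρ | Noncentrality | Power |
|---|---|---|---|
| 2 | 0.3 | 0.0625 × 52 × 2/0.7 = 9.29 | 84.8% |
| 2 | 0.4 | 0.0625 × 52 × 2/0.6 = 10.83 | 89.8% |
| 2 | 0.5 | 0.0625 × 52 × 2/0.5 = 13.0 | 94.2% |
| 3 | 0.25 | 0.0625 × 52 × 3/0.75 = 13.0 | 89.9% |
| 3 | 0.5 | 0.0625 × 52 × 3/0.5 = 19.5 | 98.0% |

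So a total of about 52 can be reached from f = 0.25, at a correlation near 0.4 with two time points or near 0.25 with three. The article gives no correlation.

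**The case against.** The best defence is that 0.25 is Cohen's f for the planned analysis. Statistical methods for primary and secondary outcomes {20a} specifies repeated measures ANOVA, and Table 1 schedules compliance at baseline, week 8 and 8 weeks after treatment. As shown above, f = 0.25 with unremarkable correlations gives about 90% power with 52 patients in total. This part stands: 0.25 is not necessarily a stray figure, and a reader who concludes that 26 per group cannot be obtained from 0.25 on any reading goes further than the document allows.

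It does not rescue the paragraph. The article states neither the metric nor the correlation. The reading leaves 8 and 9 with no role, although the text says that they were used. And f = 0.25 corresponds to d = 0.5 for two groups, which still differs from 0.89.

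A second objection also stands: the article describes 8 as a change after therapy and does not say that it is a difference between groups. If it is a within-group change, 0.89 is not the between-group effect, and writing 0.89 into the protocol would replace one unsupported figure with another.

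A third is that the matter is one of wording, since the number of patients would not change. That is true of its cost, but the wording is the trial's primary power statement, and it is wrong as written.

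**Conclusion.** The paragraph states two effect sizes that cannot both underlie one calculation. The stated 26 per group is consistent with 8 and 9 (27 or 28 recomputed, two-sided 5%, 90% power) and inconsistent with 0.25 as a standardized mean difference (about 338 per group, a roughly 12-fold gap).

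A reader might infer that the trial has only 14% power, or that 66 patients is the wrong number. The documents support neither. The 14% holds only if 0.25 is a two-group standardized mean difference, the test is two-sided and 26 per group are analysed; it becomes 17% with all 33. The figures 8 and 9 support the planned size: about 88% power with 26 completers per group and 94% with 33.

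The figures for d = 0.89 rest on 8 being a between-group difference, 9 being the SD that applies to that comparison, and a two-sided two-sample test. The first of these needs the sponsor's confirmation.

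**What to change.** First, the sponsor should confirm from the original calculation whether 8 is a between-group difference, and what 0.25 was.

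- **If 8 is a between-group difference:** remove 0.25. State that the calculation rests on a between-group difference of 8 ml/cmH2O with SD 9 (d = 0.89), in a two-sample comparison at two-sided 5%. Give power as about 88% with 26 completers per group and 94% if all 33 are analysed. Add that the smallest difference detectable with 90% power and 26 per group is about 8.3 ml/cmH2O.
- **If 0.25 was Cohen's f:** say so, state the test, the number of time points and the assumed within-subject correlation, and drop the claim that 8 and 9 were used.

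Keep the total of 66. The cost is a change of wording and, in the first case, a stated power slightly below 90% with 26 completers. No extra patients are needed.

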### Recruitment {15}

We will recruit patients through publication and distribution of posters and leaflets containing information of the study. Most of the patients are from the Department of Rehabilitation Medicine, Affiliated Hospital of Southwest Medical University. If the number of patients in rehabilitation medicine cannot meet the required number of participants in our experiment, we will continue to recruit patients with NDO referred by neurosurgery, urology, and other departments until recruitment is completed. The official start of recruitment was on 01 September 2022.

## Assignment of interventions: allocation

### Sequence generation {16a}

The random allocation table will be generated by SPSS 23.0 software, and the included cases will be randomly divided into treatment and control groups. The research coordinator is responsible for randomization, which will be carried out by simple 1: 1 draw (for each pair of patients who are recruited).

### Concealment mechanism {16b}

The random allocation table will be sealed in duplicate in an opaque envelope and stored in the third party and the main research unit, respectively. After the clinical trial is over and all the case report forms are double-checked by the participating clinical treatment units, evaluation units, and third parties, the data will be finally locked.

### Implementation {16c}

Randomization will be implemented by a research assistant who is not involved in the trial in any form. After ensuring patients fulfill inclusion criteria and informed consent forms are obtained from them, the envelopes are opened by the rehabilitation therapist specializing in rFMS and rFMS treatment is carried out.

## Assignment of interventions: blinding

### Who will be blinded {17a}

All of the trial participants, outcome assessors, and data analysts will be blinded after assignment to interventions. They only know the patient number and they don't know the specific group of patients.

### Procedure for unblinding if needed {17b}

Unblinding will be allowed under emergencies such as the incidence of serious adverse effects.

## Data collection and management

### Plans for assessment and collection of outcomes {18a}

Urodynamic examinations will be performed by the same experienced technician who has been performing urodynamic examinations for more than 5 years. The residual volume of the bladder, the Spinal Cord Injury-Quality of Life, Neurogenic Bladder Symptom Score, and pudendal nerve electromyography will be conducted by professional evaluators. The bladder diary comes from patient records.

All researchers, including the rFMS therapist, outcome assessors, data collectors, data managers, and statisticians, will undergo training before the experiment. All data will be anonymized and saved in an encryption study folder and only the study team has access to this study folder.

### Plans to promote participant retention and complete follow-up {18b}

The importance of completion of the treatment and follow-up assessment will be stressed. Patients are allowed to stop the experiment at any time during the study. If possible, the patient will be asked to complete the follow-up assessments at 8 weeks after the end of treatment. Throughout the study period, the researchers will keep in close contact with the participants if necessary.

### Data management {19}

The epidata (version 4.6) will be used to manage data. After finishing all the assessments, data will be checked by trained personnel and two people will be both processing data to ensure data accuracy.

### Confidentiality {27}

All data will be stored on the local server of the Rehabilitation Department of the Affiliated Hospital of Southwest Medical University. All data, including personal data collected, will be kept strictly confidential.

### Plans for collection, laboratory evaluation, and storage of biological specimens for genetic or molecular analysis in this trial/future use {33}

There are no plans for collection and evaluation of biological specimens in this study.

## Statistical methods

### Statistical methods for primary and secondary outcomes {20a}

We will use SPSS 23.0 statistical software for data analysis with a statistical significance level set at* p* ≤ 0.05. We will apply the chi-square test or Fisher’s exact test to analyze categorical data such as symptoms or gender. Data that is not normally distributed will be analyzed using nonparametric analysis. In addition, repeated measures ANOVA and post hoc tests will be used to analyze statistically significant differences between and within the groups.

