### Outcomes {12}

#### Primary outcome

The primary outcome is the bladder compliance measured by urodynamic testing. Bladder compliance is the relationship between a change in bladder capacity and a change in detrusor pressure (Pdet) [13]. Urodynamic examinations will be performed by the same experienced technician who has been performing urodynamic examinations for more than 5 years. The detection steps are as follows: ① The day before the examination, the patient is given a glycerin enema to clear up dry stools. The skin around the anus and perineum is prepared, and pubic hair is removed if necessary. ② On the day of the examination, the patient is placed in a supine position, the genital area is routinely disinfected, sterile towels are applied, and a 6F double-lumen manometry catheter is inserted into the bladder through the urethra and will be fixed with tape (penis for males, perineal for females). Insert an 8F balloon catheter into the rectum, inject an appropriate amount of fluid into the balloon of the rectal catheter, and place it in the patient’s rectum to a depth of about 10 cm. ③ During the measurement, the patient will take the lithotomy position. And the normal saline will fill the bladder with a perfusion rate of 50 ml/min by using a water pump. The patient will be told to cough before the start of perfusion to suppress the urge to urinate during perfusion, to cough again before the end of the assay, and to report when the patient feels the first urge to urinate and feels that the maximum cystometry volume been reached. Measure and record using the sensor-related indicators. ④ Obtain bladder compliance, abdominal pressure (Pabd), intravesical pressure (Pves), Pdet, urine flow rate (Q), and other indicators. Safe bladder capacity refers to the bladder capacity when the bladder pressure reaches 40 cmH_2_O or occurring urine leakage in the filling period [14]. And the Pdet will be measured in the urodynamic tests described above.

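### The plan for the primary outcome pairs repeated measures ANOVA with post hoc tests between and within groups, and does not say which term, contrast or visit decides the trial

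*Protocol article*

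**What the plan says.** The primary outcome is defined without a time point: "The primary outcome is the bladder compliance measured by urodynamic testing" (Protocol article, Primary outcome). The Participant timeline {13} says that compliance "will be evaluated at baseline, 8th week of treatment", and adds that "the above assessments will be followed up at 8 weeks after the end of treatment". Table 1 agrees, so there are three measurements, the first taken before allocation.

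The section Statistical methods for primary and secondary outcomes {20a} sets the significance level at p ≤ 0.05 and gives the method for outcomes over time: "repeated measures ANOVA and post hoc tests will be used to analyze statistically significant differences between and within the groups". It adds that "Data that is not normally distributed will be analyzed using nonparametric analysis", without naming the test or the rule for switching to it. Section {20b} plans no additional analyses, so no baseline-adjusted comparison appears elsewhere in the article.

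Sample size {14} assumes a change of 8 ml/cmH2O with SD 9, type I error 5% and power 90%. It arrives at 26 evaluable patients per group, or about 33 after 20% dropout.

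**The concern.** A two-group ANOVA over three visits has two terms that could carry the treatment question, the group main effect and the group-by-time interaction. Post hoc tests then add between-group comparisons at each visit and within-group changes in each arm. The text ranks none of these above the others.

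Three consequences follow.

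- The group main effect averages over all visits, including the pre-randomisation one, where the arms differ only by chance. That dilutes any treatment effect.
- If more than one test may count as the primary result, the chance of a false claim exceeds 5%.
- A within-group change is not a randomised comparison. Both arms receive tolterodine, acupuncture and bladder management, so compliance could improve in both without any effect of rFMS. A significant change in one arm beside a non-significant change in the other would then say nothing reliable about efficacy.

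A switch to an unnamed nonparametric test on the evidence of the data adds a further choice made after the results can be seen.

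**Working it through.** **Inputs.** From Sample size {14}: difference 8, SD 9 (read as the SD of change), alpha 0.05, power 0.90, n = 26 per group. Sidedness is not stated; two-sided is assumed. The correlation ρ between visits is not given; 0.3 to 0.7 is assumed, with equal variances and correlations across visits (compound symmetry).

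**The plan's own figure.** For a single comparison of two means, n = 2 × [9 × (1.960 + 1.282) / 8]² = 26.6, so 27 per group against the stated 26. Dropout: 26 / 0.8 = 32.5, so 33 as stated. The sample size thus matches one two-group comparison, with power about 0.89 at 26 per group. (The stated standardised effect of 0.25 does not match 8/9 = 0.89. That is a separate matter and is not used here.)

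**Variance.** An SD of change of 9 gives σ² = 81 / [2(1 − ρ)], so σ²(1 − ρ) = 40.5 at every ρ.

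**Group main effect.** The SD of a patient's three-visit mean is σ√[(1 + 2ρ)/3], which is 5.55, 7.35 and 10.39 at ρ = 0.3, 0.5 and 0.7. The averaged effect is (0 + 8 + 8)/3 = 5.33 if the benefit is sustained and (0 + 8 + 0)/3 = 2.67 if it is lost by follow-up.

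**Interaction (2 and 100 df).** The noncentrality is (26/2) × Σ(d − mean d)² / 40.5. For differences (0, 8, 8) or (0, 8, 0) the sum of squares is 42.67, the noncentrality 13.7 and the power 0.91. For (0, 8, 4), where the benefit halves, these are 32, 10.3 and 0.81. None of these depends on ρ.

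**Week-8 ANCOVA.** The residual SD is 9√[(1 + ρ)/2], which is 7.26, 7.79 and 8.30 at ρ = 0.3, 0.5 and 0.7.

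| ρ | Main effect, sustained | Main effect, lost | Interaction, sustained or lost | Interaction, halved | Week-8 ANCOVA |
|---|---|---|---|---|---|
| 0.3 | 0.92 | 0.40 | 0.91 | 0.81 | 0.97 |
| 0.5 | 0.73 | 0.25 | 0.91 | 0.81 | 0.95 |
| 0.7 | 0.44 | 0.15 | 0.91 | 0.81 | 0.93 |

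Beyond this range ANCOVA has 0.91 at ρ = 0.8, equal to the interaction, and 0.90 at ρ = 0.9, slightly below it. If the benefit halves, ANCOVA leads the interaction by 16 points at ρ = 0.3 and by 8 at ρ = 0.9. If 9 is instead the SD at a single visit, ANCOVA has 0.91 to 0.99 over ρ = 0.3 to 0.7 and the interaction 0.79 to 0.99 (0.66 to 0.96 if the benefit halves).

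**False positives with no true group difference** (simulation, 20,000 trials, 26 per group, three visits, ρ = 0.3 to 0.7). Either ANOVA term is significant in 9.4 to 10.1% of trials; two independent tests would give 1 − 0.95² = 9.75%. Either post-baseline between-group test is significant in 8.2 to 9.7%, and any of these four in 13 to 15%.

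**Within-group tests.** Suppose that both arms improve equally by an assumed 2, 3, 4 or 5 ml/cmH2O. A paired test with n = 26 and SD 9 then has power p = 0.19, 0.37, 0.59 or 0.78. The chance that rFMS is significant and sham is not is p(1 − p) = 0.16, 0.23, 0.24 or 0.17.

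**The case against.** The article condenses a fuller protocol, and the deciding term, the conditions for post hoc tests and the rule for non-normal data are often settled in a statistical analysis plan that is not shown here. Testing between and within groups is also common shorthand for a mixed ANOVA with one between-group and one within-patient factor. The usual treatment test in that model is the interaction, which is a valid randomised comparison and reaches 0.91, above the 90% target. Post hoc tests run only after a significant interaction, and adjusted, would hold the error near 5%; the article states neither condition but excludes neither.

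Much of this stands. It rules out several stronger readings:

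- A reader might infer that the plan would present a significant change in the rFMS arm alone as efficacy. The article nowhere says so; it only leaves that possible.
- A reader might infer that both arms start tolterodine and acupuncture at entry and are therefore expected to improve. The Medication and Acupuncture sections say that patients receive these treatments. Eligibility {10} records past treatments and does not exclude earlier use of either. The equal improvement used above is an assumption.
- A reader might infer that repeated measures ANOVA as such costs much power. That is true of the group main effect only, and the article does not say that this term decides.
- A reader might take week 8 as the stated primary visit. The article does not name one.

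The objection does not remove the point. The article commits to a method under a heading that covers the primary outcome, puts within-group beside between-group testing, and has the data choose between parametric and nonparametric tests. An analysis plan that followed this text would inherit those choices, and a better analysis is available from data already scheduled.

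**Conclusion.** The concern holds in limited form. Several tests at p ≤ 0.05 could each be called the primary result, and none is designated.

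The power cost depends on which term is used. It is large for the group main effect, at about 5 to 78 percentage points below a week-8 ANCOVA over the scenarios in the table. Against the interaction it is small, at about 1 to 6 points with a sustained or fully lost benefit and none at a correlation of about 0.8. The risk of a false claim is about 9 to 10% if either ANOVA term counts, and 16 to 24% for a misleading within-group contrast if both arms improve equally by 2 to 5 ml/cmH2O and that contrast is read as efficacy.

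These figures rest on assumed correlations, compound symmetry, two-sided tests and 9 read as the SD of change. This is a should-fix matter: the wording needs settling before unblinding, but the documents do not show that the trial would be analysed invalidly.

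**What to change.** In section {20a}, name one primary analysis: the between-group difference in bladder compliance at one stated visit, by ANCOVA or a mixed model of the two post-baseline visits, adjusted for baseline compliance and reported with a 95% CI. The end of treatment, week 8, is the natural visit, for the investigators to confirm before unblinding. Make the other visit secondary and within-group changes descriptive only. Fix the analysis scale in advance (for example, log compliance if skew is expected) in place of the switch on a normality check.

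The change needs no new patients or measurements. Its cost is a protocol amendment: recruitment began on 1 September 2022, and section {25} requires ethics re-review and updates to the registry and protocol. When the correlation between visits is high, the change brings little or no power over the interaction test; the gain is then a single, directional, interpretable contrast.

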### Eligibility criteria {10}

The inclusion criteria are as follows: ① definitely diagnosed as suprasacral SCI [10], the course of the disease is more than one month; ② age: 18–60 years old; ③ urodynamics indicates NDO [11]. The exclusion criteria are as follows: ① patients with metal implants in the lumbosacral area; ② patients with cognitive dysfunction who cannot cooperate; ③ patients with unstable vital signs; ④ those who have a history of botulinum toxin injection within 6 months or a history of bladder/sphincter surgery; ⑤ patients with unstable fractures who cannot complete urodynamics. Once patients are enrolled, we will use questionnaires to record participants’ baseline data such as age, gender, symptoms, duration, past treatments (including medications and rehabilitation), and more.

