### Intervention description {11a}

The rFMS group will receive real rFMS treatment of the sacral nerve, while the sham group will receive sham stimulation. Both groups will receive similar treatment strategies, including medication, standard urine management, acupuncture treatment, and health education.

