#### Medication

According to relevant guidelines [12], each patient will receive tolterodine with a dose of 2 mg twice a day.

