#### Acupuncture treatment

Acupuncture treatment will be performed by an experienced traditional Chinese medicine doctor who has been in acupuncture for more than 5 years. Select Tianshu, Guanyuan, Qihai, Sanyinjiao, Yinlingquan, and other acupoints to clean and disinfect each point; then acupuncture the acupoints, and leave the needle for 30 min. The acupuncture will be conducted once a day, five times a week, for 8 weeks.

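### Between-arm and within-arm tests are planned without ranking, and the within-arm test in the rFMS arm cannot separate rFMS from background care and time

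*Protocol article*

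**What the plan says.** Under Statistical methods for primary and secondary outcomes {20a}, the article states that "repeated measures ANOVA and post hoc tests will be used to analyze statistically significant differences between and within the groups". The two kinds of comparison stand side by side. The sentence does not name the group-by-time interaction and does not say which result decides.

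The background care is the same in both arms. Intervention description {11a}: "Both groups will receive similar treatment strategies, including medication, standard urine management, acupuncture treatment, and health education". Medication: "each patient will receive tolterodine with a dose of 2 mg twice a day". Acupuncture treatment: "The acupuncture will be conducted once a day, five times a week, for 8 weeks". Table 1 places medication and acupuncture in the 8-week treatment period.

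The baseline comes first. Participant timeline {13}: "Before starting the intervention, participant baseline data will be collected", with bladder capacity and detrusor pressure from urodynamics among the baseline measurements. Compliance, the primary outcome, is measured again at week 8 and 8 weeks after treatment ends.

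Eligibility criteria {10} admit patients once "the course of the disease is more than one month". Earlier medication is recorded, but no washout or stable-dose rule is stated.

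**The concern.** The first objective is the efficacy of rFMS. A before-after test inside the rFMS arm measures the total change in that arm: any rFMS effect, plus tolterodine, acupuncture, urine management and health education, plus the natural course in patients who may be little more than a month from injury. The article's own Discussion lists anticholinergic drugs and acupuncture among the routine treatments for NDO, so part of the change may well come from them. No p-value from that arm alone can separate the parts.

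At stake is how the results are read. If the rFMS arm changes significantly and the sham arm does not, a reader may take this as evidence for rFMS, although a difference in significance between arms is not a test of the difference between arms. With both tests planned and no ranking, the article contains no rule against that reading when the between-arm result is null.

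**Working it through.** **Inputs from the article, Sample size {14}.** "bladder compliance change after therapy of 8 ml per cm H_2_O with a standard deviation of 9 ml per cm H_2_O"; type I error 5% (taken as two-sided, since the side is not stated); power 90%; 26 per group, 33 after 20% dropout.

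**Inputs assumed.** The mean change due to background care and time, equal in both arms, written b. The article gives no value, so a range is used. The correlation r between baseline and week-8 compliance is also not given; 0.3 to 0.7 is used, with equal variances at the two visits.

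**Step 1: reproduce the stated sample size.** For a two-sample comparison, n per group = 2 × [9 × (1.960 + 1.282) / 8]² = 26.6, which rounds up to 27 against the stated 26. With dropout, 26 / 0.8 = 32.5, giving 33. A paired single-group calculation would need only about 14 to 15 patients. The stated size therefore fits the between-arm comparison.

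**Step 2: within-arm test in the rFMS arm when rFMS does nothing.** The paired t test has noncentrality b√n / 9 on n − 1 degrees of freedom. For n = 26 and b = 2 this is 2 × 5.099 / 9 = 1.13; for b = 4 it is 2.27.

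| Assumed b (ml/cmH2O) | P(significant), n = 26 | P(significant), n = 33 |
|---|---|---|
| 0 | 5% | 5% |
| 1 | 8.5% | 9.5% |
| 2 | 19% | 24% |
| 4 | 59% | 70% |
| 6 | 90% | 96% |

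A Bonferroni correction over the three visit pairs (α = 0.0167) still leaves 9% at b = 2 and 40% at b = 4 with n = 26.

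**Step 3: the misleading pattern.** The arms are independent, so the probability that the rFMS arm improves significantly and the sham arm shows no significant change is P(significant improvement) × [1 − P(significant)]. With n = 26 this is 2.4% at b = 0, 15% at b = 2 (0.155), 24% at b = 4 and 9% at b = 6. It falls again at large b because both arms then tend to be significant.

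**Step 4: the between-arm test.** A shift common to both arms cancels in the difference. In simulations with a common background effect, the between-arm rejection rate was 4.7% to 5.4%.

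**Step 5: power of the between-arm options, true difference 8, 26 per arm.**
- Change scores: noncentrality 8 / (9 × √(2/26)) = 3.20 on 50 degrees of freedom; power 88%.
- Week-8 value adjusted for baseline: an SD of change of 9 implies a residual SD of 9 × √((1 + r)/2).

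| Assumed r | Residual SD | Power (49 df) |
|---|---|---|
| 0.3 | 7.26 | 97% |
| 0.5 | 7.79 | 95% |
| 0.7 | 8.30 | 93% |

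**The case against.** The strongest reply is that the article never claims what this point warns against. No section rests efficacy on a within-arm test. The trial is randomised, blinded and sham-controlled with equal background care, and between and within is ordinary language for a repeated measures model with a treatment arm. All of this stands. A reader might infer that the trial intends to conclude efficacy from the rFMS arm alone, perhaps because the Sample size section speaks of a change after therapy or because the Abstract expects improvement after rFMS. The documents do not support that. A change score serves a between-arm comparison equally well, 26 per group matches the two-sample calculation and not the paired one, and the Abstract sentence is an expectation, not an analysis rule.

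A second reply is that the rates are driven by assumption. This also stands in part. The background shift is not in the article, and the rates apply only if within-arm tests are run whatever the interaction shows. If post hoc tests follow only a significant group-by-time interaction, the pattern in Step 3 cannot exceed about 5% when rFMS does nothing. The article does not say whether such a condition applies.

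A third reply is that the choice of deciding contrast can be left to the SAP or the full protocol. That would answer a complaint of pure omission. It does not answer the fact that the article commits to a within-arm significance test, which cannot address the objective however it is detailed later. Within-arm change remains legitimate as description, for example of maintenance from week 8 to follow-up.

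**Conclusion.** The point holds in a limited form, at minor to moderate severity. The planned within-arm test in the rFMS arm mixes rFMS with background care and time and should carry no weight for efficacy. This follows from the design and needs no numerical assumption.

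Its size does rest on assumptions: a common background shift of 2 to 4 ml/cmH2O, an SD of change of 9, and within-arm tests not conditional on the interaction. Under these, the rFMS-arm test is significant in 19% to 59% of trials at 26 per arm with no rFMS effect. Patients already on an antimuscarinic at baseline would alter the size of the shift but not the conclusion.

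A reader might go further and infer that the trial cannot show an rFMS effect, or that its efficacy result is biased. Neither follows: the randomised contrast is unaffected, keeps its 5% error rate and is what the trial is sized for.

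**What to change.** Replace the sentence on repeated measures ANOVA and post hoc tests with a statement on these lines: the primary analysis is the between-arm difference in bladder compliance at week 8, adjusted for baseline compliance, and the efficacy conclusion rests on this contrast. Report within-arm changes as means with confidence intervals, without efficacy tests.

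The cost is an edit to the text and one degree of freedom (49 in place of 50 at 26 per arm). Baseline compliance is already in Table 1, so no extra patient, visit or measurement is needed. The adjustment also brings power above the stated 90% for assumed correlations of 0.3 to 0.7, where the change-score analysis falls just short at 88%.
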